### Sample Size Estimation

With a teacher population of approximately 45,000 in Alberta and Nova Scotia, using a web-based script [62], we estimate that the sample size needed for our prevalence estimates with a 95% CI and 3% margin of error for moderate-to-high stress, burnout, likely GAD, likely MDD, and low resilience among teachers in Alberta and Nova Scotia is 1043. Based on the response rates achieved for the Text4Hope and Text4Mood programs in Alberta [35,63,64], we expect a maximum of 20% survey completion rate for the Wellness4Teachers program. Thus, to achieve the 1043 completed surveys at baseline, we expect to enroll 5515 teachers on the Wellness4Teachers program within 12 months.

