### Wellness4Teachers Program

Wellness4Teachers is a self-subscription daily supportive text message intervention program designed to address stress, burnout, anxiety, and depression, and to build resilience and improve professional satisfaction in teachers. The Wellness4Teachers program is powered by the ResilienceNHope web-based application [40] and provided by the Global Psychological eHealth Foundation [41]. ResilienceNHope is an evidence-informed e–mental health program that incorporates cognitive behavioral therapy based on daily supportive messages (mobile text or email), weekly mental health literacy information, web-based mental health self-assessments, and other mental health resources to help address part of the mental health literacy and the psychological treatment gap for individuals and communities globally. The Wellness4Teachers application will deliver one-way (noninteractive) psychological intervention messages to mobile phones. Subscribers will be made aware of the noninteractive nature of the supportive messaging program through the welcome and introductory message they receive upon subscribing to the program. They will also be offered the phone number of the mental health crisis service for their province or region to call if they are in crisis. The daily supportive messages delivered through the Wellness4Teachers program were crafted by psychiatrists, mental health therapists, and psychologists based on the cognitive behavioral therapy principles. The messages were further reviewed by the lead author, who is an education specialist, before they were built into the Wellness4Teachers program. Different messages will be received daily from a bank of messages. Examples of the text messages are as follows:

Deep breathing is a skill. You may need to practice it often and for more than 5 minutes to feel calmer. When you are feeling stressed or tense, shrug your shoulders up to your ears, hold for 5 seconds, release and repeat 2 more times. https://www.youtube.com/watch?v=cOOd-wlMMRg.

As a teacher, it is very important for your well-being to spend time talking, laughing, and sharing with your colleagues. If you feel overwhelmed, take time to do something kind for yourself such as a cup of tea, or nature walk.

Visualize yourself coping with the current challenging student behavior or workload. See yourself confidently facing these challenges. You can do it! No matter the challenges.

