### Outcomes and Measures

Clinical outcomes will be assessed using validated screening scales for self-reported symptoms, including Perceived Stress Scale (PSS-10; a score of ≥10 indicates a likely moderate or high stress) [55], the 7-item GAD scale (GAD-7; a score of ≥10 indicates likely generalized anxiety disorder) [56], the Patient Health Questionnaire-9 (PHQ-9; a score ≥10 indicates likely MDD) [57], and the Brief Resilience Scale (BRS; mean scores ranging from 1.00 to 2.99 indicate low resilience, from 3.00 to 4.30 suggest normal resilience, and from 4.31 to 5.00 suggest high resilience) [58,59].Validated scales have been chosen to better understand self-reported symptoms and potential symptom severity and to screen for the likely presence of psychopathology. These scales are not intended as diagnostic tools but instead are to identify risk factors and early symptoms of potential mental disorders such as depression and anxiety disorders. In addition, we will assess burnout using the Maslach Burnout Inventory (MBI) [60]. The MBI-Educators Survey will be used in this case, which is a version of the original MBI for use with educators, including teachers, administrators, other staff members, and volunteers working in any educational setting [61]. The primary outcome measures will be prevalence of moderate-to-high stress, burnout, likely GAD, likely MDD, and low resilience at baseline in subscribers of Wellness4Teachers. Other primary outcome measures will be changes in prevalence of moderate-to-high stress, burnout, likely GAD, likely MDD, and low resilience as well as changes in mean scores on the PSS-10, MBI, GAD-7, PHQ-9, and the BRS from baseline to 6 weeks, 3 months, and 6 months. Secondary outcome measures will include sociodemographic, clinical, and professional correlates of moderate-to-high stress, burnout, likely MDD, likely GAD, and low resilience among subscribers of Wellness4Teachers at baseline. An exploratory outcome will be a measurement of the adoption of the Wellness4Teachers program by teachers in Alberta and Nova Scotia. This will be assessed by measuring the proportion of the target population (teachers in Alberta and Nova Scotia) who subscribe to the daily supportive text messages.

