### Limitations of the Study

First, the self-report scales used to assess mental health variables such as likely MDD, although standardized, are not meant to be diagnostic. Second, it is possible that participants’ demographics in the study may not reflect the demographics of the teachers’ population in Alberta or Nova Scotia, and therefore the study findings may not be generalizable to all teachers in the 2 provinces. Furthermore, web-based surveys with survey links delivered through text messages usually achieve a response rate of less than 20% [42,63,64,75-78], and therefore it is possible that we may not achieve our desired sample size. Lastly, the supportive text messages will be delivered for 6 months, and the outcome measures will be evaluated at 6 weeks, 3 months, and the end point of 6 months. It is unclear what the effects of the intervention would be if it were prolonged. It is also unclear if the benefits of the intervention would wane with the cessation of the daily supportive text messages. These limitations notwithstanding, this study is the first to examine the prevalence and correlates of stress, burnout, anxiety, and depression among teachers in the provinces of Alberta and Nova Scotia in Canada, aided by a text message program. This study is also the first globally to assess if daily supportive text messages delivered through the Wellness4Teachers program can reduce the prevalence and severity of stress, burnout, anxiety, and depression, and improve resilience among elementary and high school teachers. The findings would therefore be of interest to policy makers, especially those working in the education sector.

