### Conclusion

The outcome of this study will establish the prevalence and correlates of the common risk factors for psychological disorders under study in teachers in Alberta and Nova Scotia. The study will have a significant impact on the management of stress, burnout, anxiety, depression, and low resilience among teachers. If the findings are positive, the Wellness4Teachers program can be promoted as a tool to support the mental health of teachers in Canada and internationally. The study outcome will also compliment policy decision-making for health care resource allocation in support of the education sector.

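### The ±3% margin is stated for all teachers in Alberta and Nova Scotia, but it is sampling error under random response, and the data come from self-selected subscribers

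*Protocol article*

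**What the plan says.** The Sample Size Estimation section starts from the whole teaching workforce: "With a teacher population of approximately 45,000 in Alberta and Nova Scotia". It derives the "sample size needed for our prevalence estimates with a 95% CI and 3% margin of error" and ties the result to that workforce, ending "low resilience among teachers in Alberta and Nova Scotia is 1043". It then expects at most 20% of subscribers to complete the survey and plans to enrol 5515.

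Other sections name different populations for the same quantity:

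- **Study Aims (Textbox 1):** prevalence among elementary and high school teachers in the two provinces.
- **Outcomes and Measures:** the primary prevalence outcome ends "low resilience at baseline in subscribers of Wellness4Teachers".
- **Wellness4Teachers Program:** people enter through a "self-subscription daily supportive text message intervention program designed to address stress, burnout, anxiety, and depression". The sentence goes on to name resilience and professional satisfaction as further aims.
- **Study Design:** teachers are invited by advertisement through teacher and school board organisations, and the surveys go to subscribers.
- **Limitations of the Study:** participants' demographics may differ from those of teachers, so "the study findings may not be generalizable to all teachers in the 2 provinces".
- **Conclusion:** the study "will establish the prevalence and correlates" in teachers of the two provinces.

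**The concern.** A margin of error from a random-sample formula says how far an estimate is likely to lie from the population value when every member had a known, equal chance of being sampled. Here a teacher reaches the data in two voluntary steps: subscribing, then answering. Either step may depend on how stressed, burnt out, anxious or depressed the teacher is, which is what the survey measures. If so, the estimate is centred on a value other than the teacher prevalence, and a larger sample does not bring it closer.

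Baseline prevalence is a primary outcome. The Hypothesis section sets it against figures from other jurisdictions, and the Discussion offers the findings to policy makers. A reader who takes the Sample Size Estimation section at its word would treat a reported figure ±3 points as the range for all teachers in the two provinces.

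The limitations paragraph does not remove this risk. It speaks of demographics, not of selection on mental-health need. It treats low response as a threat to reaching the sample size, not as a source of bias. It leaves the ±3% unqualified.

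**Working it through.** **Inputs.** From Sample Size Estimation: N = 45,000 teachers, 95% confidence, margin d = 0.03, stated n = 1043, completion at most 20%, planned enrolment 5515. The assumed prevalence is not stated ("using a web-based script [62], we estimate that the sample size needed"). I take p = 0.5, the usual worst case, as an assumption.

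**1. The plan's own figure.**
- n0 = z²·p(1−p)/d² = 1.96² × 0.25 / 0.03² = 1067.1
- With finite population correction: n = n0 / (1 + (n0 − 1)/N) = 1067.1 / (1 + 1066.1/45,000) = 1042.4, rounded up to 1043

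The figure reproduces. It is the simple-random-sample formula with all 45,000 teachers as the population.

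**2. The margin at 1043 completers.**
- Without correction: 1.96 × √(0.25/1043) = 3.03 points
- With correction for 45,000: 3.00 points

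**3. How completers are reached.**
- Subscribing: 5515/45,000 = 12.3% of teachers
- Completers: 1043/45,000 = 2.3% of teachers

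Neither step is a random draw.

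**4. How much selection would use up the margin (illustration).** Let R be the chance that an affected teacher ends up among the completers, divided by the chance for an unaffected teacher. At 2.3% inclusion this is practically an odds ratio. The documents give no value for R, so R is an assumption, as is true prevalence p.
- Expected estimate = pR / (pR + 1 − p)
- R for a shift from p to p′ = [p′/(1 − p′)] / [p/(1 − p)]
- Shift of +3 points: p = 0.3 gives (0.33/0.67)/(0.30/0.70) = 1.15; p = 0.5 gives 0.53/0.47 = 1.13
- Shift of −3 points: p = 0.3 gives (0.27/0.73)/(0.30/0.70) = 0.86; p = 0.5 gives 0.47/0.53 = 0.89
- R = 1: no shift. Only then does ±3% also describe accuracy for teachers.
- R = 1.5: +9.1 points at p = 0.3, +10.0 points at p = 0.5

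With standard error 0.03/1.96 = 0.0153, a bias of 3 points in either direction equals 1.96 standard errors. A nominal 95% interval then covers the teacher prevalence about 50% of the time.

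**5. If subscribers are the target.** With N = 5515, the sample needed for ±3 points is 1067.1 / (1 + 1066.1/5515) ≈ 894. At 1043 completers the margin is 3.03 × √((5515 − 1043)/5514) = 2.73 points. For the population named in Outcomes and Measures, 1043 is therefore more than enough for sampling error. Non-response of at least 80% among subscribers would remain.

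**The case against.** The strongest reply is that a margin of error means sampling error by convention. The Sample Size Estimation section never says that respondents are a random sample or that the estimates are unbiased. Outcomes and Measures already restricts the primary outcome to subscribers, the limitations concede weak generalisability, and the word used in the Conclusion is closing prose, not a design parameter. This lowers the weight of the point but does not remove it. The section does more than quote a margin: it names teachers in the two provinces as the population and corrects for their number. The caveat sits elsewhere, concerns demographics, and is followed at once by the stronger claim in the Conclusion.

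Four stronger readings are tempting, and the documents do not support them:

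- **The estimates will be too high.** A reader might infer this from the program's purpose, but the documents fix neither size nor direction. The two steps could offset each other: the Introduction itself says that stressed or burnt-out teachers may be unable to complete mindfulness programs, so lower response among the most distressed is also plausible. The content of the advertisement is not given.
- **The margin is wrong for either population.** For subscribers, 1043 is conservative, at about ±2.7 points.
- **Precision by province is inadequate.** The Statistical Analysis section promises descriptive statistics by province and claims no provincial margin.
- **The lack of weighting is an error.** This is a condensed article, and weighting may be specified in a full protocol or analysis plan that is not shown.

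**Conclusion.** The point holds as a mismatch between a stated precision and the population to which it is attached. The arithmetic behind 1043 is correct. The ±3% is sampling error under random response, and nothing in the design makes it the accuracy of prevalence among all teachers in Alberta and Nova Scotia. The sections also disagree on whether the prevalence concerns teachers or subscribers.

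The size of the resulting error is unknown. The inclusion ratios of 1.13 to 1.15 (0.86 to 0.89 for a downward shift) rest on an assumed prevalence of 30% to 50%. They show only that modest selection would be enough to use up the 3 points, not that such selection will occur. The change is worth making because it limits what the study can claim for a primary outcome and costs little. It does not call for a different sample size.

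**What to change.** 1. In Sample Size Estimation, state that ±3% is sampling error only, assumes random response, and does not apply to all teachers in the two provinces.
2. Align Study Aims, Outcomes and Measures, Sample Size Estimation and the Conclusion on prevalence in responding subscribers, and remove the claim that the study "will establish the prevalence and correlates" among teachers.
3. In Limitations of the Study, name self-selection and non-response related to mental health as a source of bias of unknown direction.
4. As a supplement, where teacher totals by province, school level, gender or experience can be obtained, report estimates weighted to those totals beside the unweighted ones. The survey already collects demographic and professional variables. Whether the partner organisations can supply the totals is an assumption.

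The cost is a narrower claim, some rewording and one further analysis step. Weighted intervals would be somewhat wider: with an assumed design effect of 1.2 to 1.5, the margin becomes 3.00 × √1.2 = 3.3 to 3.00 × √1.5 = 3.7 points. Weighting addresses the demographic imbalance that the limitations admit. It does not remove selection on distress itself, so items 1 to 3 are needed in any case.

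### The enrolment target of 5515 does not follow from 1043 surveys at 20% completion (that gives 5215), and the 20% used is a stated ceiling

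*Protocol article*

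**What the plan says.** All of the planning is in the protocol article, Methods, Sample Size Estimation. It starts "With a teacher population of approximately 45,000 in Alberta and Nova Scotia" and seeks "prevalence estimates with a 95% CI and 3% margin of error" for each of the five baseline prevalences. An online calculator gives 1043 completed surveys. From experience with two earlier text-message programs, "we expect a maximum of 20% survey completion rate for the Wellness4Teachers program". The section then concludes: "Thus, to achieve the 1043 completed surveys at baseline, we expect to enroll 5515 teachers on the Wellness4Teachers program within 12 months".

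The Limitations section returns to the response rate. It says that web surveys whose links are sent by text message "usually achieve a response rate of less than 20" per cent, and "therefore it is possible that we may not achieve our desired sample size".

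**The concern.** The enrolment figure is presented as the consequence of the two numbers before it, 1043 and 20%, yet the division gives a different result. No dropout or other allowance is mentioned in the section to explain the difference.

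The rate used is also an upper limit. Dividing the required surveys by the highest rate expected gives the smallest enrolment that could suffice. The section nevertheless presents the result as the number that will deliver 1043 surveys, although the Limitations section expects the rate usually to be lower.

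This is the only planning calculation in the article, and it supports baseline prevalence, which the Outcomes and Measures section lists as primary. At stake are the correctness of a published target and the realism of the stated ±3%.

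**Working it through.** **Inputs.** From Sample Size Estimation: population N = 45,000, 95% confidence (z = 1.96), margin d = 0.03, 1043 completed surveys, completion at most 20%, enrolment 5515. The assumed prevalence is not stated; I take p = 0.5, the usual worst case, and it reproduces the stated number.

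**Step 1: the 1043.**
- Without finite-population correction: n0 = z² p(1 − p) / d² = 1.96² × 0.25 / 0.03² = 1067.1.
- With correction: n = n0 / (1 + (n0 − 1)/N) = 1067.1 / (1 + 1066.1/45,000) = 1042.4, rounded up to 1043.

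The plan's figure is reproduced.

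**Step 2: from 1043 to enrolment.**
- 1043 / 0.20 = 5215, not 5515. The difference is 300, or 300/5215 = 5.8%.
- In reverse, 1043 / 5515 = 18.9% completion, and 5515 × 0.20 = 1103 surveys.

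**Step 3: could a dropout allowance explain 5515?** The Wellness4Teachers Program section reports 10% dropout in an earlier program and expects less than 15% here. The sample-size section cites neither.
- 10%: 5215 / 0.90 = 5795, or 5215 × 1.10 = 5737.
- 15%: 5215 / 0.85 = 6136, or 5215 × 1.15 = 5998.
- 5%: 5215 / 0.95 = 5490. This is close but not equal, and the document gives no 5% allowance.

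None of these yields 5515.

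**Step 4: margin at lower completion.** Half-width = 1.96 × √(p(1 − p)/n) × √((N − n)/(N − 1)), with p = 0.5 and n = enrolment × completion rate. The 15% and 10% rates are my illustrations; the document says only that rates are usually below 20%.

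| Completion | Surveys from 5515 | Margin | Surveys from 5215 | Margin | Enrolment needed for 1043 |
|---|---|---|---|---|---|
| 20% | 1103 | ±2.91% | 1043 | ±3.00% | 5215 |
| 15% | 827 | ±3.38% | 782 | ±3.47% | 6954 |
| 10% | 552 | ±4.15% | 522 | ±4.27% | 10,430 |

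With 5515 enrolled, ±3% at p = 0.5 holds down to 18.9% completion. With 5215 enrolled, it holds only at 20%.

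**Step 5: prevalences away from 50%.** The Wellness4Teachers Program section reports 88.0% moderate-to-high stress among new subscribers to an earlier program. With p = 0.88 and 552 surveys, 1.96 × √(0.88 × 0.12/552) × √(44,448/44,999) = ±2.69%, still within 3% at 10% completion. For anxiety (46.5%) and depression (52.1%) in the same group, the margin is about ±3.4% at 15% completion and ±4.1% at 10%.

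**The case against.** The case on the other side has four parts.

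- **The slip is in the safe direction.** The target exceeds what the stated inputs require, and at 20% completion it gives better than ±3%. This stands. A reader might infer that the arithmetic error is what puts the ±3% at risk. It is not: the error adds a reserve of 300 enrolments, and the risk comes from using a ceiling as the divisor.
- **The shortfall is disclosed.** The Limitations section says the desired sample size may not be reached. This stands as disclosure. What remains is that the admission does not alter the enrolment target or the stated precision.
- **Not every rate below 20% loses ±3%.** A reader might infer that any completion rate under the ceiling misses the stated precision. The figures do not support that. With 5515 enrolled, rates from 18.9% to 20% still meet it at p = 0.5, and a prevalence as far from 50% as the 88.0% for stress meets it even at 10%. For outcomes near 50% the loss at 15% or 10% is real.
- **Lowering the target would do harm.** Replacing 5515 by 5215 and changing nothing else would remove the only reserve against low response. This stands and shapes the fix below.

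It is also tempting to call 5515 a typing slip for 5215. That is plausible, but nothing in the document shows it.

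**Conclusion.** The point holds as a minor numerical correction. The target of 5515 does not follow from 1043 surveys and 20% completion, which give 5215; 5515 corresponds to 18.9%, and no rate or allowance in the document bridges the gap. Because 20% is described as a maximum and lower rates are said to be usual, the target is close to a best-case minimum. If completion were 15% or 10%, the worst-case margin with 5515 enrolled would be ±3.38% or ±4.15% instead of ±3%.

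These margins rest on p = 0.5, a population of 45,000 with finite-population correction, and illustrative completion rates. The required number of completed surveys, 1043, is correct. No analysis or decision rule depends on the enrolment figure, and the achieved precision will follow from the surveys actually returned. The study's conclusions are not threatened.

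**What to change.** In Sample Size Estimation:

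1. Reconcile 1043, 20% and 5515. The better choice is to keep 5515 and state the 18.9% completion rate behind it, which fits a ceiling of 20% and preserves the small reserve. The alternative is to give 5215 as the enrolment at 20%.
2. Call the figure a minimum enrolment.
3. Add one sentence with the worst-case margin (p = 0.5, finite-population correction) at lower completion, using one enrolment figure throughout. For 5515: ±2.9% at 20%, ±3.4% at 15% and ±4.15% at 10%. For 5215: ±3.0%, ±3.5% and ±4.3%. Say that the 15% and 10% rates are illustrative and that margins are narrower for prevalences away from 50%.

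The cost is one reconciled figure and one or two sentences. No extra enrolment is required; the only downside is a slightly less favourable stated precision.

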### Statistical Analysis

Quantitative data from the surveys will be analyzed using SPSS (version 25, IBM Corp) [65]. Descriptive statistics will be provided for demographic, clinical, and burnout-related variables based on the province of residence. Cross-tabular analyses using the chi-square test will explore the differences between elementary and high school teachers with respect to demographic, clinical, and professional variables. Descriptive characteristics will be presented as numbers and percentages, and a 2-tailed *P*≤.05 will be used to determine statistical significance for all analyses. We will use the chi-square test and logistic regression analysis to identify demographic, clinical, and work-related correlates of anxiety, depression, stress, low resilience, and burnout for elementary and high school teachers separately. Furthermore, we will assess the impact of the Wellness4Teachers program in reducing moderate-to-high stress, burnout, likely GAD, likely MDD, and improving resilience among Wellness4Teachers subscribers by assessing the mean changes in these parameters from baseline to 6 weeks, 3 months, and 6 months using the 2-tailed paired *t* test. To assess the effects of the intervention against a control group, we will choose a defined period of 3 months during the study period (eg, from the beginning of November 2022 to the end of January 2023) and compare the prevalence and mean scores on standardized scales for stress, burnout, anxiety, and depression at 6 weeks for subscribers who have received the daily supportive text messages for 6 weeks (intervention group) to the baseline prevalence and mean scores on the same scales for new subscribers during the period (control group). Surveys with more than 50% missing responses will be omitted from data analysis. For the included survey responses, there will be no imputation for missing data, and the analysis and results will be based on completed survey data.

We will analyze qualitative data (obtained by audio recording and transcribing responses from key informant interviews) using thematic analysis with NVivo (version 9; QSR International). The results will be reported as themes and subthemes supported by verbatim quotes.

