### Hypothesis

We hypothesize that the prevalence of stress, burnout, symptoms of anxiety and depression, as well as low resilience among teachers in Alberta and Nova Scotia would be comparable to those reported in other jurisdictions [8,66].

We also hypothesize that factors such as gender, sex, age, marital status, number of years teaching, grade of teaching, and school type (elementary vs high school) will have an association with burnout and other psychological disorders in teachers [67-72].

Finally, we hypothesize that the Wellness4Teachers program will reduce the prevalence and severity of stress, anxiety, depression, burnout, and low resilience symptoms among teachers by at least 20% [43]. This specific hypothesis is based on related research findings. In the 2 RCTs conducted in Ireland and Canada, there was a greater than 20% reduction in depression symptom scores in the intervention group compared to the control group [73,74]. Furthermore, for the Text4Hope program in Alberta, there was a greater than 20% reduction in anxiety symptom scores in subscribers at 6 weeks and 3 months [36,37].

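### The search for correlates runs about 50 to 60 tests at an unadjusted P≤.05, so at least one false-positive correlate is very likely, yet the results are framed as a hypothesis and as something the study will establish

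*Protocol article*

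**What the plan says.** The point concerns the baseline correlates only, not the changes over time.

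- **Analysis.** Statistical Analysis says: "We will use the chi-square test and logistic regression analysis to identify demographic, clinical, and work-related correlates of anxiety, depression, stress, low resilience, and burnout". The sentence goes on to require this for elementary and high school teachers separately.
- **Threshold.** The same section says "a 2-tailed *P*≤.05 will be used to determine statistical significance for all analyses".
- **Hypothesis.** The second hypothesis lists seven personal and professional factors as examples, school type among them, and predicts that these "will have an association with burnout and other psychological disorders in teachers". No direction of association is given.
- **Tier.** Outcomes and Measures says "Secondary outcome measures will include sociodemographic, clinical, and professional correlates of moderate-to-high stress" and the other four conditions. That section applies the exploratory label only to adoption of the program. The study objectives box lists correlates under the main objectives.
- **Claim.** The Conclusion says "The outcome of this study will establish the prevalence and correlates of the common risk factors for psychological disorders".

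The article gives no ordering, lead outcome or adjustment within the correlates family. It does not say which pattern of results would count as support for the hypothesis.

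**The concern.** A stated significance rule is applied to a wide grid of factor, outcome and school-type combinations, and the output is presented as inferential. With that many tests at the nominal level, some significant correlates are to be expected even if none is real. Because the two school types are analysed apart, a chance finding can also appear as a correlate specific to one school type.

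The article offers its results to policy and decision makers in education. A chance correlate reported as established could therefore influence which teachers are thought to be at risk. With no decision rule for the hypothesis, its authors would also have to choose after seeing the data how much significance, and where, counts as support.

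**Working it through.** **The plan's own figures.** The article states neither a number of correlate tests nor a family-wise error rate, so there is no figure of its own to reproduce on this point. Its sample size of 1043 does reproduce: 1.96² × 0.25 / 0.03² = 1067.1, and 1067.1 / (1 + 1066.1/45,000) = 1042.4, rounded up to 1043. That size serves the precision of the prevalence estimates. It does not limit false positives among the correlates.

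**Inputs from the article**
- Level: 0.05, two-sided, for every analysis (Statistical Analysis).
- Outcomes: five at baseline, namely moderate-to-high stress, burnout, likely MDD, likely GAD and low resilience (Outcomes and Measures).
- Strata: two, elementary and high school (Statistical Analysis).
- Factors: seven are named under Hypothesis, as examples. School type cannot be tested within a school-type stratum, which leaves six, or five if gender and sex are merged. The abstract's Results paragraph names four, of which three can be tested within a stratum.

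**Count, with one test per combination**
- 6 × 5 × 2 = 60
- 5 × 5 × 2 = 50
- Abstract's list: 3 × 5 × 2 = 30
- Testing school type itself against the five outcomes adds 5, giving 65, 55 or 35.

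Further clinical and work-related variables would add to these counts. Using both chi-square and logistic regression could give a second P value per combination; neither addition is counted here.

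**Expected false positives if no factor is related to any outcome.** This is 0.05 × k and does not depend on correlation between tests: 3.0 (k = 60), 2.5 (k = 50), 1.5 (k = 30).

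**Chance of at least one, independent tests,** 1 − 0.95^k:
- k = 60: 95.4%
- k = 50: 92.3%
- k = 30: 78.5%

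**Chance of at least one, correlated tests.** The article gives no correlations, so these are assumed. Null z statistics were simulated (100,000 replicates, strata independent, rejection at |z| > 1.96):

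| Factors | Correlation between factors | Outcome correlation 0 | 0.5 | 0.8 |
|---|---|---|---|---|
| 6 (60 tests) | 0 | 95% | 91% | 81% |
| 6 (60 tests) | 0.5 | 91% | 84% | 70% |
| 5 (50 tests) | 0 | 92% | 87% | 74% |
| 5 (50 tests) | 0.5 | 87% | 79% | 65% |

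A separate simulation used chi-square tests on binary data, with an assumed 521 teachers per stratum, gender and sex almost collinear, age and years of teaching strongly correlated, and outcome correlations from 0 to 0.9. It gave 82% to 94%.

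**Narrower readings of what would support the hypothesis, under the same null**
- At least one significant association with burnout: 10 tests give 1 − 0.95^10 = 40%, and 12 tests give 1 − 0.95^12 = 46%. With correlated factors the simulations give about 37% to 41%.
- Every listed factor showing at least one hit among its 10 tests: 0.401^5 = 1.0% for five factors and 0.401^6 = 0.4% for six, if independent.

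**The case against.** **The tempting stronger reading.** A reader might infer that the hypothesis would very probably be confirmed by chance alone. The article does not support that. It never says that one significant result anywhere confirms the hypothesis. The 65% to 95% is the chance of any hit in the grid, which is a different quantity. On the narrower readings, chance support ranges from about 37% to 46% down to 1% or less. This part of the objection stands.

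**The count is not a floor.** The list of factors is open-ended and the abstract's version is shorter, so 50 to 60 is a reading of the Hypothesis section and not a fixed family. Chi-square followed by regression may be a screen and then a model, not two rounds of testing. This also stands. The shorter list still gives 78.5% for independent tests.

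**The analysis plan may deal with it.** Adjustment within a secondary family is often left to a statistical analysis plan, which is not shown. That would answer a silence, but the article is not silent: it sets the level for all analyses. An analysis plan that adjusted the threshold would sit awkwardly with that sentence.

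**The family is already low in the hierarchy and descriptive in spirit.** The correlates are secondary, the comparison of elementary with high school teachers is described as exploring differences, and the article concedes limited generalisability. The global null is also a worst case, since the article cites earlier literature for these associations. These points limit the severity. They do not remove the mismatch, because for correlates the verb is *identify*, the associations are posed as a hypothesis, and the Conclusion promises to establish them.

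**Conclusion.** The point holds in a limited form. Under the stated rule, and if no factor is related to any outcome, 2.5 to 3.0 false correlates are expected from the 50 to 60 within-stratum tests. At least one is very likely: 92% to 95% for independent tests, and roughly 65% to 95% over the assumed correlations. The nominal level for a single test is 5%.

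The calculation assumes one test per combination, independent strata and the factor list under Hypothesis. The expected count does not depend on the correlations. If some associations are real, fewer null tests remain and the number of false ones falls accordingly.

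The fault is the combination of an unadjusted threshold for all analyses, inferential framing, and no exploratory label or decision rule. How often chance would lead to the hypothesis being declared supported cannot be stated, because the plan gives no rule. The family is secondary and baseline-only, so this should be corrected, but it does not affect the assessment of the intervention.

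**What to change.** 1. In Outcomes and Measures and in Statistical Analysis, label the correlates analysis exploratory and report it as odds ratios with 95% CIs.
2. In Statistical Analysis, where significance is quoted for correlates, apply a false-discovery-rate adjustment, for example Benjamini-Hochberg at 5%. It should cover all factor-by-outcome-by-school-type tests, including those of school type itself, and be stated as an exception to the blanket threshold. For 55 to 65 tests the strictest step is 0.05/55 = 0.00091 to 0.05/65 = 0.00077; later steps are less strict.
3. In the Conclusion, replace *establish* for correlates with *describe* or *explore*.

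Naming a single lead outcome such as burnout, with Holm's correction, would supply a decision rule for the hypothesis, but it is optional and for the investigators to decide. The article lists the five outcomes without ranking them. If this route is taken, the family must include school type: 12 within-stratum tests plus one for school type make 13, with a first threshold of 0.05/13 = 0.0038.

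The cost is a few sentences and a routine adjustment of P values, with no new data. The downside is that fewer correlates will be called significant.
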